#### Exclusion criteria

Participants who are undergoing active treatments (surgery, chemotherapy and radiation) as well as those less than 6 months post active treatment. Likewise, those individuals with cognitive impairment and unable complete the questionnaires will be excluded. Participants with known metastatic disease will also be excluded from the study. The participant will be withdrawn from the study if they develop cancer recurrence or metastases during the study period.

### Recruitment

The study will recruit participants who are breast cancer survivors within 3 years of diagnosis and at least 6 months post primary treatments. Eligible participants will be randomly allocated to immediate intervention or delayed intervention groups in a 1:1 ratio after completion of informed consent. The participants will be recruited from Breast cancer care service, Western Health Sunshine campus in Melbourne. Recruitment strategies will include public media (poster advertising or flyer) and individual contact introduced by their physician [35]. All participants have to be approved by their physician for engagement in the physical activity program of this research and the screening process will be conducted before obtaining consent.

The study will commence at Western Health Sunshine campus following ethical approval from Melbourne Health Human Research Ethics Committee (MH HREC) and Western Health research governance authorization [36]. Based on our power calculation we aim to recruit 64 participants.

### Randomisation

The study design is a two-armed RCT with a crossover design. Sequence generation will be conducted by simple randomisation following patient informed consent. The participants will be randomly allocated to either IIG or DIG in 1:1 ratio by computerised number generator. Allocation concealment by enclosing the allocation in sealed envelopes will be used to prevent selection bias [37]. The allocation concealment will be conducted by a third party to prevent researchers from affecting group assignment. The participants in both groups will be prescribed a self-directed physical activity for 24 weeks. The IIG will receive MI from week 1 to week 12, whereas DIG will receive the same MI intervention from weeks 13 to 24.Allocation concealment technique will be applied in process of randomisation. During weeks 1 to week 12, theIIG will perform self-directed physical activity and receive MI. On the other hand, the DIG will perform self-directed physical activity without MI. During week 13 to week 24, DIG will continue self-directed physical activity with MI. Whereas IIG will perform physical activity but will no longer be given MI.

## Methods of intervention

### Self-directed physical activity

Participants will perform a 24-week period of self-directed, pedometer controlled physical activity [38, 39]. All participants will be given a step-count tracker devise (Fitbit Alta HR) and investigators will explain the prescribed pedometer-based activity to participants. Fitbit Alta HR is a wearable gadget and can be used to monitor step count. The participants’ activity engagement will be accompanied by individual face-to-face and phone call MI [22]. Participants will be taught how to operate the Fitbit and will be taken on a 10 min walk to experience a moderate level of exertion.. At week 1 (baseline or T1), all participants will be prescribed to assess and record their activity using the Fitbit monitoring device through its application via computer or smartphone to establish their baseline physical activity volume by step count. Following this, they will be advised to perform their activity on their own pace as tolerated and will wear the Fitbit during the daytime or when they are available for physical activity throughout the 24 weeks. Individual participants will be advised and motivated to gradually increase their daily steps on physical activity at moderate intensity exertion or at their perception of taking some efforts but can talk during physical activity (the recommendation by the department of health, Australian government) [40] during face-to-face and over the phone MI. The participants will be advised for safety during physical activity. They will be suggested to stop physical activity if adverse symptoms occur such as chest pain or pain down to arms, dizziness, difficulty breathing, unusual rapid heart rate, and sever fatigue. The researcher will suggest to the participant to inform their family members and take a mobile phone with them before they go out to exercise. They will be also advised to take record of their daily steps in their notebook. All participants will be informed that the researcher will track the participants’ step count and tracker usage time via Fitbit connect application. Individual average daily step count, and activity level will be assessed at baseline (T1), week 12 (T2), and week 24 (T3).

### Motivational interviewing

MI will be used in encouraging participants through open-end questions, friendly and supportive communication and induction of behavioral changes [22, 24]. Each MI will be conducted through four phases of conversation comprising: 1) Engage, 2) Focus, 3) Evoke, and 4) Plan [22]. The study will use the dialog of MI guided by Mentha Counselling and will be conducted by a counsellor who experienced MI There will be a 20 min face-to-face in week 1 and three phone MI sessions (15 min) at weeks 2, 4 and 9 for IIG. For DIG this will take place at weeks 12, 13, 15 and 20.

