**Methods:**

The study will recruit 64 female breast cancer survivors within 3 years of diagnosis and at least 6 months post primary treatments at Western Health Sunshine Hospital, Melbourne, Australia. They will be randomly allocated to immediate intervention (IIG group) or delayed intervention groups (DIG group) in a 1:1 ratio. All participants will be given a wearable device (Fitbit Alta HR) and undertake self-directed physical activity for 24 weeks and will receive MI for 12 weeks (IIG; during week 0 to week 12 and DIG; during week 13 to week 24). Participants’ daily step count and the changes of immune cell functionality will be assessed at the beginning (week 1: T1), week 12 (T2) and week 24 (T3) of the program. Physical activity adherence will be assessed at T2 and T3. Participants will also complete four questionnaires assessing exercise self-regulation (BREQ2), exercise barrier and task self-efficacy, mental health (DASS-21) and QoL (FACT-B) at three time points (T1 to T3). Linear-mixed models will be used to assess the relationship between physical activity volume by step counting and mental health (DASS-21), QoL (FACT-B), immune biomarkers, self-regulation (BREQ2) and self-efficacy at T1, T2 and T3;between 2 groups.

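### The delayed group's first motivational interview is listed at week 12, inside its MI-free period and in the week of T2; the immediate group's falls in the baseline week, and nothing orders assessment before MI

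*Protocol article*

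**What the plan says.** The Motivational interviewing section gives the sessions by week. For IIG: "There will be a 20 min face-to-face in week 1 and three phone MI sessions (15 min) at weeks 2, 4 and 9 for IIG". The entry on the delayed group reads: "For DIG this will take place at weeks 12, 13, 15 and 20".

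Three other places give MI periods instead of sessions. The Randomisation section states: "The IIG will receive MI from week 1 to week 12, whereas DIG will receive the same MI intervention from weeks 13 to 24". It adds that in weeks 1 to 12 DIG does its self-directed activity with no MI. The abstract gives "IIG; during week 0 to week 12 and DIG; during week 13 to week 24", and the Study design section gives the same windows.

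Assessments are at week 1 (T1), week 12 (T2) and week 24 (T3). This holds for DASS-21 and FACT-B, for the immune markers and for step count (outcome sections and Table 1). The blood collection section uses the same T1, T2 and T3. For steps, the Self-directed physical activity section says: "At week 1 (baseline or T1), all participants will be prescribed to assess and record their activity using the Fitbit monitoring device". This record is to set the baseline activity volume, and advice on activity comes after it.

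On allocation, the Recruitment section says: "Eligible participants will be randomly allocated to immediate intervention or delayed intervention groups in a 1:1 ratio after completion of informed consent".

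**The concern.** The sections disagree on when DIG's MI starts. On the session list, DIG receives MI within what the Randomisation section treats as its control period, and in the very week in which the control value is measured. By T3 both arms have had MI, so T2 is the only post-baseline time at which the randomised groups differ in whether they have had MI at all.

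T2 also has two roles in a crossover. For DIG it closes the period without MI and opens the period with it. A T2 value taken after the first session makes the control period look better and the MI period look worse.

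IIG has a parallel problem at T1. Its only face-to-face session, a contact at which participants are to be encouraged to walk more, falls in the week whose Fitbit record is the baseline. DIG has no such contact that week, so the two baselines may not be measured under the same conditions.

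**Working it through.** **Inputs**
- IIG session weeks: 1, 2, 4, 9. DIG session weeks: 12, 13, 15, 20 (Motivational interviewing).
- Stated DIG window: weeks 13 to 24 (abstract, Study design, Randomisation).
- T1, T2, T3: weeks 1, 12, 24 (outcome sections, Table 1).

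**Step 1: sessions against the stated window.** Of DIG's four sessions, 13, 15 and 20 lie in weeks 13 to 24 and 12 does not. One of four is outside the window.

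**Step 2: sessions against assessments.** IIG's week 1 coincides with T1. DIG's week 12 coincides with T2. No other session falls in an assessment week.

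**Step 3: offset between the arms.** 12 − 1 = 13 − 2 = 15 − 4 = 20 − 9 = 11 weeks, the same in every position. The stated windows start 13 − 1 = 12 weeks apart if IIG's starts at week 1, as in Randomisation. A 12-week shift of IIG's list would read 13, 14, 16, 21. The steady 11-week offset suggests a deliberate schedule, with the first session tied to the T1 visit in one arm and the T2 visit in the other, more than a single mistyped week. It does not show which section is right.

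**Step 4: is there an order within those weeks?** The only ordering statement places activity advice after the baseline step recording. It concerns steps at T1 only. Nothing comparable covers the T1 questionnaires or blood, or any measurement at T2.

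**Step 5: exposure of a weekly step mean.** Assume a seven-day mean over week 1 or week 12 and a session on day k of that week. Then 7 − k of the 7 days follow the session: 6 of 7 if k = 1, none if k = 7. This is a share of days, not an effect size.

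**Step 6: direction.** Let Δ be the full MI effect, a the fraction of it already present in IIG's T1 value, and b the fraction already present in DIG's T2 value. Ignoring period effects:
- between arms at T2, unadjusted: Δ becomes (1 − b)Δ;
- between arms, change from T1 to T2: Δ becomes (1 − a − b)Δ;
- within DIG, MI-period change minus control-period change: Δ becomes (1 − b)Δ − bΔ = (1 − 2b)Δ.

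For small positive a and b, each contrast moves toward zero. The documents give no value for a or b.

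**The case against.** The strongest reply is that assessing first and then interviewing at the same visit is the natural reading, that the constant offset fits it, and that an article may leave visit order to the full protocol or to its schedule figure, which is not shown. That stands as far as it goes: the text does not show any assessment being done after MI. It does not remove the contradiction about DIG's start week. Nor would assessing first within a visit protect a step mean whose days run on past the session.

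A second reply is that one short conversation will hardly move same-day questionnaires or blood. This is fair, and these are the primary outcomes. Steps are secondary and more exposed.

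A third is that the Analysis of data section relates step volume to outcomes and does not define a baseline-adjusted T2 difference. That is true, but any estimate of MI's effect that uses the randomisation must draw on T2 or on changes to or from it.

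A reader might also infer more than the documents support:
- **That participants know their arm at T1.** Allocation follows consent, but the text does not say when the envelope is opened relative to the T1 measurements.
- **That IIG's MI starts before baseline.** The week 0 in the abstract and Study design is probably a period label; no week-0 session is listed.
- **That the harm is beyond repair.** Daily step counts are recorded, so days before a session could be averaged afterwards where data exist. Questionnaires and blood have no such remedy.
- **That the loss can be priced.** If b = 0.25, the sample-size equivalent would be 1/0.75² = 1.78, but 0.25 is a pure assumption and has little bearing on the primary outcomes.
- **That unequal follow-up biases the comparison.** The last session is 12 − 9 = 3 weeks before T2 in IIG and 24 − 20 = 4 weeks before T3 in DIG. No consequence of that one-week difference is shown.

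**Conclusion.** The contradiction is certain: one of DIG's four sessions lies outside the stated MI window, inside the period described as free of MI, and in the week of T2. That IIG's first session shares the week of T1 and the baseline step record is equally plain. Contamination of the IIG baseline and of DIG's end-of-control value is possible, not demonstrated, because the text neither orders nor misorders the measurements and the sessions.

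If it occurs, the bias runs toward no difference, provided that MI has an early effect of the same sign as its later one. It is most plausible for step counts. The placing of activity advice after the baseline recording protects T1 steps only in part, since a week-1 session can still overlap the recording days. For questionnaires and blood taken on the day of a session the effect is probably small. No size can be derived from the documents.

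**What to change.** 1. Reconcile the abstract, Study design, Randomisation and Motivational interviewing sections so that they give one start of MI for each arm. This review takes no position on which week is right.
2. Whatever weeks are kept, state that the T1 questionnaires, blood and baseline step days are completed before allocation is revealed and before any MI.
3. State that the T2 questionnaires, blood and the days entering the T2 step mean are completed before DIG's first session.

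The cost is protocol wording, a visit-order instruction and a short delay, about a week, between consent and opening the envelope. The Fitbit handover may have to be separated from IIG's first MI session, which could mean a further in-person contact. If that is not feasible, the minimum is to assess first within the visit and to average only step days that precede the session.

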### Blood collection and storage

Approximately 20 ml of blood will be collected via a venipuncture at T1, T2 and T3 for both groups. Whole blood will be collected into a tube containing anticoagulant and centrifuged immediately after collection or on the same day approximately 7 h later.

Isolation of peripheral blood mononuclear cells (PBMCs) by density gradient configuration using Ficoll-Paque will be used for immune cell functions. PBMCs will be stored in refrigerator not longer than 1 day and then use flow cytometry to assess the composition of the isolated PBMC populations.

### Method of data collection and outcome measurements

#### Primary outcomes

##### Psychological health and QoL

Levels of stress, depression and anxiety will be assessed using the DASS 21 [41]. The DASS21 has been validated for breast cancer survivors and has good reliability [42]. In addition, the FACT-B version 4 [43] will be used to measure QoL. This cancer specific questionnaire is well validated and has good reliability and measures physical, social/family, emotional and functional well-being aspects and breast cancer specific conditions [43, 44]. Participant will complete these instruments at baseline; week 1 (T1), week 12 (T2), and week 24 (T3).

##### Immune function

PBMC cells (white blood cells) will be isolated from blood and PBMC assessed for changes at the cellular level by flow cytometric analysis [45] at baseline; weeks 1 (T1), 12 (T2), and 24 (T3). Cell surface markers, CD40, CD80, CD83, CD86, MHC-I, MHC-II, CD14, CD16, CD206, CD209 will be assessed by flow cytometry technique [45] to determine the changes after the program. In addition, the ratio of type 1 and type 2 T helper (Th1/Th2) cytokines secreted by monocytes and T cells will be determined to understand any cellular changes following exercise activity.

#### Secondary outcomes

##### Average daily step count

Participants will record their own daily steps through the Fitbit Alta HRapplication, upload their step count on their computer or smartphone and send the data to the researcher by email or phone call weekly. They can also record their steps from the tracker in a provided notebook. Researchers can track an individual’s daily step count via Fitbit Alta HR application on a computer or smartphone. The average daily step count will be calculated at baseline at each of the 12 weeks of the intervention program.

##### Adherence in step tracker usage

The participants’ adherence to self-directed physical activity will be evaluated by their compliance by wearing the Fitbit Alta HR. The adherence rate of fitness tracker usage can be an indicator for exercise program feasibility in breast cancer patients [46]. The adherence will be defined as step count tracker wearing time with data capture (daily hours and the number of wearing days) [46]. The mean of daily hours and number of wearing days per week will be calculated at the end of week 12 and week 24 of self-directed physical activity period [31].

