#### Analysis of data

Baseline descriptive statistics (mean, standard deviation for continuous data and percentage for categorical data) will be used to describe the distribution of personal data and variables between two groups of participant (e.g., age, breast cancer health history, body compositions, and blood pressure). Independent T-test will be used to compare means for continuous data and the Pearson Chi square will be used for testing the difference in distribution of a categorical variable at baseline [49].

Linear-mixed models will be used to identify the relationship between physical activity volume by step counting and mental health (DASS-21), QoL (FACT-B), self-regulation (BREQ2) and self-efficacy at T1, T2 and T3; the relationship between activity volume by step counting and immune biomarker changes at T1,T2, and T3. The models will also be used to control for the effect of covariates or confounding factors and to manage for missing data.

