## Discussion

Self-directed physical activity in this clinical trial is considered a feasible practice in breast cancer survivors. More specifically, the combination of self-monitoring (step count) and MI have been shown to be important strategies for long-term adherence to physical activity behaviour in people living with cancer. This trial, will examine the efficacy of these health behaviour change techniques in self-directed physical activity. This is an important issue because this is a potentially low cost intervention which could be applied and implemented widely if successful. This study is guided by the Self-Determination Theory [32] and Social Cognitive Theory [26]. We anticipate that those who adhere to the program will be more intrinsically motivated at the end of the trial in comparison to those who do not. We will also explore whether the initial motivational orientation predicts adherence to the physical activity program. In addition, we would anticipate that successful adherence to the physical activity program will be associated with higher levels self-efficacy believes and reduced number of barriers to be physically active.

The primary outcomes of this study focuses on both psychological and physiological changes which can translate positively for their breast cancer clinical outcomes. The study expects the enhancement of their QoL, psychological health and immune biomarkers in 12 to 24 weeks self-directed physical activity by pedometor application combining 12 weeks motivational interviewing.

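### Activity adherence is scored by Fitbit wear time, but the wear instruction lets women choose how long to wear it, so the score measures device use and wear hours are not comparable between women

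*Protocol article*

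**What the plan says.** All references are to the protocol article.

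- **Wear instruction (Self-directed physical activity).** After the week-1 baseline recording, participants "will wear the Fitbit during the daytime or when they are available for physical activity throughout the 24 weeks". No minimum hours or days are given.
- **Adherence (Adherence in step tracker usage).** The construct is stated first: "adherence to self-directed physical activity will be evaluated by their compliance by wearing the Fitbit Alta HR". The operational definition follows: "The adherence will be defined as step count tracker wearing time with data capture (daily hours and the number of wearing days". The summary is also fixed: "The mean of daily hours and number of wearing days per week will be calculated at the end of week 12 and week 24". Steps, intensity and active minutes play no part.
- **Labels.** That section's heading and Table 1 describe the measure as use of the tracker or pedometer. The abstract says that physical activity adherence is assessed at T2 and T3. The Discussion builds expectations on it, for example "We anticipate that those who adhere to the program will be more intrinsically motivated at the end of the trial".
- **Steps (Average daily step count).** "The average daily step count will be calculated at baseline at each of the 12 weeks of the intervention program". No wear condition is stated.
- **Models (Analysis of data).** Step count is the activity-volume variable related to DASS-21, FACT-B, immune markers, self-regulation and self-efficacy. Covariates are allowed but not named.
- **Wear data.** Participants are told that "the researcher will track the participants’ step count and tracker usage time via Fitbit connect application", so wear time is available alongside steps.

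**The concern.** The instruction and the score do not fit together. The instruction treats two very different wear patterns as equally acceptable, and the score then counts hours of wear as if more hours meant more adherence to the activity programme. Two women who both do what they were told can receive very different scores for reasons unrelated to how active they are.

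Two things are at stake. First, physical activity adherence is in the trial's title, and wear is the only measure of it that the article defines. The Discussion's questions (whether initial motivation predicts adherence, and whether adherence goes with intrinsic motivation and self-efficacy) would be answered for device use instead. Second, steps are the exposure in models of the primary outcomes. Steps taken with the device off are never recorded, so unequal wear puts error into that exposure. If wear is unrelated to the outcomes, the error would mainly weaken a dose-response slope. If wear is related to mood, fatigue or motivation, the bias could go either way.

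**Working it through.** There is no figure in the plan to reproduce: the article gives no wear times, step counts or step target. The check sets the provisions side by side and then illustrates the size with assumed inputs.

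**1. Hours.** Take two women with the same activity, one wearing the device 1 h a day for her walk and one wearing it 12 h a day. Both follow the instruction. Their hours scores differ by 12 / 1 = 12-fold, with no difference in activity.

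**2. Days.** If both walk every day, both log 7 wearing days out of 7. The days component therefore does not separate them; the distortion lies mainly in hours.

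**3. Steps, same activity.** Let recorded steps = W + b × (H − 0.5), where W is the steps in a 30-minute walk, b the background steps per hour and H the hours worn. Assumed ranges, not from the documents: W from 2,000 to 4,000 and b from 200 to 400. The two corners of the range are:

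| W | b | H = 1 | H = 12 | Step ratio | Hours ratio |
|---|---|---|---|---|---|
| 4,000 | 200 | 4,000 + 200 × 0.5 = 4,100 | 4,000 + 200 × 11.5 = 6,300 | 1.54 | 12 |
| 2,000 | 400 | 2,000 + 400 × 0.5 = 2,200 | 2,000 + 400 × 11.5 = 6,600 | 3.00 | 12 |

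For a milder contrast of 8 h against 12 h, the hours ratio is 12 / 8 = 1.5. Steps go from 4,000 + 200 × 7.5 = 5,500 to 6,300 (ratio 1.15), or from 2,000 + 400 × 7.5 = 5,000 to 6,600 (ratio 1.32).

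**4. Ranking an active against an inactive woman.** An all-day wearer who takes no walk records b × 12, that is 200 × 12 = 2,400 or 400 × 12 = 4,800 steps. The daily walker who wears the device 1 h records 4,100 or 2,200. On hours, the inactive woman always ranks higher (12 against 1). On steps, the order is right in the first case (4,100 against 2,400) and wrong in the second (2,200 against 4,800). Hours carry no information on activity here. Steps carry some, distorted by wear.

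**5. Can it be repaired at analysis?** Only in part. Wear time is tracked and can be modelled, but steps taken off-wrist are lost. A minimum-wear rule added later would discard days from women who followed the second wear option.

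**The case against.** The strongest reply is that device use and activity are already separate outcomes. The section heading and Table 1 name tracker use, steps have their own row, and the article presents tracker use as an indicator of programme feasibility. On that view only loose labelling remains. This stands in part: reporting wear as device compliance would need little change. It does not remove the point, because the text states that adherence to the activity is evaluated by wear, the abstract and Discussion use it in that sense, and no alternative is defined.

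Several stronger readings are tempting but not supported:

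- *Steps are averaged without regard to wear.* The article states no valid-day rule or wear covariate, but excludes neither. A condensed article commonly leaves this to the full protocol or analysis plan.
- *Step counts reflect device use rather than activity.* They measure activity during wear and are open to bias from unequal wear, which is a weaker statement.
- *Women are told to wear the device only when exercising.* That is one permitted pattern, not the instruction.
- *Adherers and non-adherers will be misclassified.* The Discussion voices an expectation; no cut-off and no model containing adherence is given.
- *Visits without step data will drop out of the models.* The article says only that "The models will also be used to control for the effect of covariates or confounding factors and to manage for missing data". How missing steps are handled is not described, so a loss cannot be inferred.
- *Motivational interviewing raises wear and so biases the arm comparison.* This is possible because the interviewing is timed differently by arm, but nothing in the documents shows it.

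**Conclusion.** The point holds for the adherence outcome. As written, the score measures device wear, and its hours component is not comparable between women who all comply with the instruction; wearing days are affected much less. For steps the conclusion is narrower: they remain a measure of activity, but the flexible instruction leaves them open to a wear bias that analysis can only partly correct.

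The size cannot be derived from the documents. The 12-fold difference in hours and the 1.5- to 3.0-fold difference in steps rest on an assumed 1 h against 12 h contrast and on assumed walking and background step rates. At 8 h against 12 h they shrink to 1.5-fold and 1.15- to 1.32-fold. How many women would choose short wear is unknown. Both measures are secondary outcomes, but steps also serve as the exposure for the primary outcomes, so the matter deserves correction before data are collected.

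**What to change.** 1. Give one wear instruction, all waking hours, from the baseline week onward, so that baseline and later assessments are recorded under the same conditions.
2. Report hours and days worn only as device compliance, and use that label in the abstract, the outcome section, Table 1 and the Discussion.
3. Define physical activity adherence from recorded steps, on days that meet a minimum wear time set and justified in advance. If the measure refers to each woman's own baseline, record that baseline before any motivational interviewing. The immediate group has its face-to-face session in week 1, the same week in which baseline steps are taken. An early effect of that session would raise its baseline and understate its later adherence.
4. Include the already tracked wear time in the models that use steps.

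The cost is small: changed participant wording, changed definitions and one covariate, plus possibly a baseline recording moved ahead of the first interview. The drawbacks are a somewhat greater wear burden and the exclusion of some low-wear days.
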